# Evaluating an online support package delivered within a disability unemployment service: study protocol for a randomised controlled feasibility study

**DOI:** 10.1186/s40814-015-0010-6

**Published:** 2015-04-10

**Keywords:** Depression, cCBT, Guided self-help, Online, Unemployment, Bibliotherapy, Low mood, Stress, Anxiety, Disability

## Abstract

**Background:**

Mental health problems such as anxiety and depression are known to be higher in those who are unemployed. Cognitive behavioural therapy (CBT) is a recognised support for people with such problems and can improve the ability of people to get back to work.

**Methods/design:**

Participants with symptoms of low mood will be recruited from the disability employment service, Remploy. Participants will receive either immediate or delayed access to an online CBT-based life skills intervention, the “Living Life” package. The primary end point will be at 3 months when the delayed group will be offered the intervention. This feasibility study will test the trial design and assess recruitment, retention, acceptability and adherence, as well as providing efficacy data.

**Discussion:**

The study will inform the design and sample size for a future full randomised controlled trial (RCT) which will be carried out to determine the effectiveness of the online package in improving mood and employment status.

**Trial registration:**

Current Controlled Trials ISRCTN10316077.

## Background

Mental health problems such as anxiety, distress and depression are known to be more common in those who are unemployed [1], with lasting effects on mood in the long term, even after re-entering employment [2]. Unemployment rates are higher among those with disabilities, and therefore this may be a group that is vulnerable to experiencing poor mental health, particularly low mood. The National Institute for Health and Clinical Excellence (NICE) recommends cognitive behavioural therapy (CBT) for mild to moderate depression [3], and this treatment has an evidence base for use in back to work settings [4]. Traditional CBT consists of 12–20 1-h sessions with a mental health expert and can be delivered in primary care settings [5]. However, it is difficult to provide this *high-intensity* specialist CBT (HI CBT) due to the large volume of people with depression needing treatment. In order to increase access to CBT, low-intensity (LI) CBT in the form of bibliotherapy (online or paper based) can be successful in improving symptoms in low-risk individuals whose condition is not complex [6,7]. NICE [3] and Gellatly et al. [8] recommend that including guidance/support in using bibliotherapy and cCBT significantly improves outcomes for those with depression using these approaches. Crucially, the support does not need to be delivered by a mental health or CBT expert, and the focus can be on supportive monitoring. The current study aims to evaluate a novel online resource that encompasses online books, training modules, worksheets and reminder emails that can be used as a tool for those aiming to get back to work.

### Remploy

Remploy is the leading provider of disability employment services in the United Kingdom. It supports those with physical and/or complex problems that affect employment. Remploy offers training and support to 2,500 people per annum through its Scottish branches. Of these, around one in four will have experienced stress or low mood at some point. Currently, support is offered both directly and also by using referrals to other organisations. Usually individuals who are out of work are referred to Remploy by their local job centre or other organisation. The usual procedure when a new referral occurs is for an initial orientation meeting to take place. Candidates then receive weekly or fortnightly support from a case worker and they are supported into, and after they have entered, employment up to a maximum of 6 months post-work (and up to 2 years in-work support).

This will be the first study to evaluate cCBT self-help resources specifically for depression in those seeking employment delivered with LI support/guidance in this type of back to work environment. Our project draws on current NICE guidelines and offers the possibility of increased access to psychological therapy with the support of employment advisors. The “Living Life” online package will be delivered by Remploy and will include those currently attending the NHS as well as those who are not.

### The Living Life website

The Living Life online package contains eight core sessions that teach a range of CBT-based life skills [9]. The Living Life content is drawn from that of the successful and widely used www.llttf.com website but is delivered via a password-protected separate website containing the course plus linked reading and worksheet materials. The majority of the sessions will be completed in the Remploy offices; however, participants will have the option of completing and/or revising sessions on their home computer if they have one. Each session focuses on a different common problem faced by people when they feel low or anxious. The class content is the following: *1: Why do I feel so bad?, 2: I can’t be bothered doing anything, 3. Why does everything always go wrong?, 4: I’m not good enough: (low confidence), 5: How to fix almost everything, 6: The things you do that mess you up, 7: Are you strong enough to keep your temper?* and *8: 10 things you can do to help you feel happier straight away.* Additional physical health sessions are available including “Reclaim your life (from illness and disability)”, “Stop smoking in 5 minutes” and “Fix your drink problem in 2 days”. The package is designed to encourage an individualised plan to be made at the end of each session using a Plan, Do, Review structure [9]. Each session consists of slides, audio, worksheets and a linked booklet that summarises the topic and includes work tasks to facilitate practice at home. The package offers guided CBT for depression delivered over a series of online modules. There are currently no equivalent packages using the same model of delivery. This accessibility is reinforced by the language used. The resources use everyday terms and avoid professional terminology, i.e. the “life skills training” instead of “CBT” and “low mood and stress” rather than “depression and anxiety”. The way of communicating CBT used is highly accessible [10] and effective [11,12]. The language used in the online package includes everyday terms to describe symptoms such as stress, distress and low mood rather than the more formal diagnostic terms depressive disorder, depression and anxiety, etc. Although non-English language versions of the courses are available, the English language version is used in the current study to facilitate support by Remploy staff. The aim is to be inclusive and for the online resource to be appealing to participants who are being recruited through Remploy.

### Aims

This project aims to determine the feasibility of a randomised controlled trial (RCT) investigating an online CBT-based life skills resource for people who are seeking work and attending Remploy. It is an unfunded study to establish viability of applying for a substantive later funded RCT.

The aim of this study is to recruit people experiencing symptoms of depression. We will include both those with clinically diagnosed major depression as well as those with raised mood scores. We will describe the population in detail in terms of mood severity and clinical diagnosis (if known). The research questions of the study are outlined below.

### Research questions

Primary question:Is the study design feasible—is it possible to recruit from Remploy, randomise participants and collect data at baseline, 3 months and 6 months?

Secondary questionsb.To what extent will participants adhere to the intervention?b.Is the Living Life package satisfactory/acceptable to participants?c.How many participants will be needed for a sufficiently powered future RCT? (Efficacy data at 3 and 6 months will be used for the future sample size estimation).

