## Methods/design

### Overview

This is a feasibility study to test the possibility of delivering the Living Life (LL) online life skills resource in Remploy. In this RCT, 50% of participants will be randomly allocated to the immediate group (IA) and will receive LL immediately. The remaining 50% of participants will be allocated to the delayed access control (DAC) group. Both arms receive treatment as usual. The primary end point is 3 months at which point the control arm will be provided with access to LL if they wish. Monitoring will continue up to a 6-month final exit point.

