### Procedure for recruitment and study setting

All new candidates will be informed of the study, and their Remploy case loader (support worker) will provide a study information pack and consent form. The potential participant will be asked to bring the consent form to their meeting the following week if they wish to take part in the study. The researcher’s contact details will be on the information sheets to allow candidates to ask questions about the study (meaning the consent given will be informed consent). The Remploy staff can also answer any questions required. Taking up or declining the study will not affect the usual support received.

On attendance at the Remploy Office for the second appointment, completed consent forms will be collected by administration staff. Participants will then hand in their baseline questionnaires to the administration staff. The administration staff will mark up the participants’ case notes as being in the study and pass a treatment allocation envelope to the case loader. The sealed allocation envelopes will have been prepared remotely by the researcher and will be selected in the presence of the participant from a box to reveal the group allocation. Envelopes will state which course they have been enrolled in (1—immediate, 2—delayed). Those allocated to the LL group will be given details of how to access the online resources. Participants will work through the online modules in the Remploy offices either on their own or as part of a group with a trained Remploy facilitator, the delivery type for each participant will be recorded by Remploy. It will not be possible for the caseloader, participant or researcher to be blind to the group allocation.

All participants will receive supportive encouragement from a trained member of staff while they use the intervention. TAU participants will be given access to Living Life after the 3 month follow-up data has been collected. The “Living Life” intervention is password protected. However, in order to identify contamination at the 3-month follow-up, participants will be asked to detail any support they have received for their mood since entering the study.

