### Follow-up data collection

The main follow-up point will be at 3 months with an additional follow-up assessment at 6 months. The data will be used to:Determine the proportion of people taking up the LL intervention, adherence to the intervention and follow-up rates.Describe the difference in proportion of people in work at 12 weeks between the LL group and the TAU control group or if not in work the number of interviews attended and job submissions made (measuring motivation).Describe the subsequent number (frequency) and total (days) off work over 3 months and 6 months in both arms comparing within group comparisons from baseline, and between-groups at 3 and 6 months.Describe and compare impact on mood, social function and satisfaction at 3 months and 6 months in both arms comparing within group comparisons from baseline, and between-groups at 3 and 6 months. This data will be used for the future sample size calculation.

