### Statistical analyses

Baseline characteristics will be summarised for all participants as well as for the IA and DAC groups separately. Participant uptake and adherence to the online intervention, defined as the number of online sessions completed and the number of support sessions participants took part in, as well as data follow-up rates, will be summarised and presented as percentages.

To assess efficacy, repeated measures analysis will be carried out using an intention to treat approach by means of a linear mixed effects model with the time (baseline, 3 months, 6 months) and group (control, intervention) main effects and their interaction as fixed effects, and participant as a random effect. Models will be adjusted for age, gender and antidepressant use at baseline. Tukey post-hoc comparisons will be carried out with a familywise error rate of 5%. These models will be used to estimate and test the statistical significance of the within-group differences between time points and the between-group differences at each time point. Finally, a power calculation will be carried out to determine the required sample size for a future RCT.

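### The 6-month between-arm difference compares immediate with delayed access, so it should not supply the treatment effect for the future trial's sample size

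*Protocol article*

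**What the plan says.** Under Overview the protocol article sets the design: "The primary end point is 3 months at which point the control arm will be provided with access to LL if they wish". The section on recruitment procedure repeats the crossover: "TAU participants will be given access to Living Life after the 3 month follow-up data has been collected". The Abstract also says that the delayed group is offered the package at 3 months.

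Three sections then use the 6-month comparison:

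- Research questions, in the question about the size of a future trial: "Efficacy data at 3 and 6 months will be used for the future sample size estimation".
- Follow-up data collection, for mood, social function and satisfaction: comparisons within groups from baseline and "between-groups at 3 and 6 months. This data will be used for the future sample size calculation".
- Statistical analyses, in the paragraph on efficacy: a linear mixed model with "time (baseline, 3 months, 6 months) and group (control, intervention) main effects and their interaction as fixed effects", used to estimate and "test the statistical significance of the within-group differences between time points and the between-group differences at each time point".

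The Participants section also explains the 50 + 50 recruitment target by the wish to compare the arms at both 3 and 6 months.

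The document does rank the visits: "The main follow-up point will be at 3 months with an additional follow-up assessment at 6 months". It does not say that the effect used for planning comes from 3 months alone, or that the 6-month contrast has a different meaning.

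**The concern.** Up to 3 months the arms differ by Living Life plus usual support against usual support alone. After that the delayed arm may use the package as well. The 6-month difference therefore answers a different question, namely what having access three months earlier is worth. The plan keeps the same two group labels, calls the result efficacy data and sends it to the sample size calculation.

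Sizing a later trial is a stated purpose of this study. An attenuated difference used as a planning effect would make that trial larger than it needs to be. A 6-month difference near zero could also be read as a fading effect when the controls had simply caught up.

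**Working it through.** **Is there a figure to reproduce?** No. The document gives no sample size for the future trial that rests on an effect, and it states no target effect, standard deviation or power. The 100 participants here are a recruitment target (50 + 50) without a power calculation. The size of the problem can therefore only be illustrated.

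**Step 1: what each contrast estimates.** Let D be the effect of Living Life against usual support at 3 months. Suppose that it persists in the immediate arm, and that by 6 months the delayed arm has gained a share u of it.

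- Expected difference at 3 months: D - 0 = D.
- Expected difference at 6 months: D - uD = (1-u)D.

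If the effect in the immediate arm has faded to a fraction f of D by 6 months, the expected difference is (f-u)D. That is smaller still, and reversed if u exceeds f.

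**Step 2: effect on a sample size.** For two means with equal allocation and SD 1, n per arm = 2(z for alpha + z for power)^2 / d^2. Replacing d by (1-u)d multiplies n by 1/(1-u)^2, whatever d is:

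- u = 0: 1/1^2 = 1 (no inflation)
- u = 0.25: 1/0.75^2 = 1.78
- u = 0.5: 1/0.5^2 = 4

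**Step 3: illustration.** Assumed, not in the document: two-sided alpha 5%, power 80%, standardised effects d of 0.3, 0.5 and 0.8. At d = 0.5 the 3-month contrast gives 2(1.960 + 0.842)^2 / 0.25 = 62.8, so 63 per arm.

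| Assumed d | n per arm, 3-month contrast | 6-month contrast, u = 0.25 | 6-month contrast, u = 0.5 |
|---|---|---|---|
| 0.3 | 175 | 311 | 698 |
| 0.5 | 63 | 112 | 252 |
| 0.8 | 25 | 44 | 99 |

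Using both visits does not remove the problem. With d = 0.5 and u = 0.5, the simple average of the two contrasts is (0.5 + 0.25)/2 = 0.375, which gives 112 per arm instead of 63.

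**Step 4: does the document give a value for u?** No. Access for the delayed arm is optional, so u could be zero. On the other hand, the Participants section admits only people willing to take up the package and excludes those unwilling or unable to use it, so some uptake is what the design expects. The question about other support, meant to detect contamination, is placed at the 3-month follow-up and does not cover planned use between 3 and 6 months.

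**The case against.** The strongest reply is that the document nowhere says that the 6-month between-group mean difference will be the planning effect. The analysis section promises only a power calculation, without naming an effect, standard deviation or visit. Data from two visits also supply variances and correlations, which are proper inputs. Three months is named as the primary end point. The time-by-group interaction lets the 3-month contrast be estimated on its own, so later crossover does not distort it.

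Much of this stands. The 3-month estimate is sound, and the harmful use is permitted rather than spelled out. But Follow-up data collection lists between-group comparisons at both visits among the data for the sample size, and Research questions calls both efficacy data. Ranking the visits does not undo that instruction.

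It can also be said that intention to treat makes the 6-month contrast valid. It is valid, for immediate against delayed access. The two arms are defined in those terms under Overview, so labelling the result that way fits the design.

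A reader might go further and infer four things that the document does not support:

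- That the 6-month difference is necessarily biased towards zero. This needs an effect, its persistence and uptake by the delayed arm, and uptake is optional.
- That the 55% adherence threshold gives u = 0.55 and hence roughly fivefold inflation. That figure, under Determining the feasibility of the study design, is the share of people completing at least four of eight modules. It is neither delayed-arm uptake nor a share of effect recovered.
- That a null 6-month result would end the programme. The feasibility criteria are recruitment, adherence, acceptability and follow-up; none uses efficacy.
- That every 6-month test must be barred. Correct labelling is enough.

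**Conclusion.** The point holds in a conditional form. The plan treats "the between-group differences at each time point" as efficacy results at 6 months as well as at 3, and makes the 6-month comparison an input to the future sample size, although by then the control arm has been offered the intervention. As an estimate of Living Life against usual care, the 6-month difference is attenuated if the package works, its effect persists and delayed participants use it.

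The inflation of a sample size based on it is then 1/(1-u)^2: nil at u = 0, about 1.8 at u = 0.25 and 4 at u = 0.5. The formula follows from the design and the persistence assumption; every value of u is assumed. The 3-month contrast is unaffected. This is a stated rule rather than a detail left to an analysis plan, and it bears on one of the study's own secondary questions.

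**What to change.** 1. In Research questions, Follow-up data collection and Statistical analyses, state that the efficacy contrast and the treatment-effect input for the future trial come from the 3-month comparison only.
2. In the same sections, label the 6-month between-arm result as immediate versus delayed access, and report beside it the proportion of the delayed arm that started Living Life. Uptake is already to be summarised; say explicitly that this covers the delayed arm after 3 months.
3. State that the 6-month data inform retention, standard deviation, within-person correlation and change within the immediate arm.
4. In Participants, align the rationale for 50 + 50, so that the 6-month comparison is not presented as equivalent to the 3-month one.

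The cost is wording in four sections, with all planned assessments kept. The study gives up a 6-month claim of efficacy against usual care, which its design cannot support. Recruitment was still under way at publication, with 20 participants entered, so the change could be made before analysis.

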## Methods/design

### Overview

This is a feasibility study to test the possibility of delivering the Living Life (LL) online life skills resource in Remploy. In this RCT, 50% of participants will be randomly allocated to the immediate group (IA) and will receive LL immediately. The remaining 50% of participants will be allocated to the delayed access control (DAC) group. Both arms receive treatment as usual. The primary end point is 3 months at which point the control arm will be provided with access to LL if they wish. Monitoring will continue up to a 6-month final exit point.

### Participants

The aim is to recruit 100 participants in total for this feasibility study, 50 intervention participants and 50 control participants to allow for comparison at the 3-month follow-up point and 6-month exit point. We will recruit males and females aged 16 +.

*Inclusion criteria:* Participants will be willing to take up the offer of LL and appropriate for usual Remploy support—and with no active risk to self at initial Remploy assessment (this is not routinely investigated, but if suicidality is disclosed at the initial assessment, the individual will not enter the study). Individuals must be able to register on the website, read and understand the LL resources via the internet or DVD; at home or in the Remploy office.

*Exclusion criteria:* Individuals will be excluded if they are unwilling or unable to use the LL approach and/or if they are at active risk of suicide, identified in which case usual care (referral to GP) will occur as is normal Remploy practice.

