### Benefits to participants

Participation within this research study will allow adults who are out of work and experiencing mild to moderate symptoms of low mood to use CBT-based educational online modules aimed at addressing these, and other, issues. Research has provided us with empirical evidence that the proposed approach is effective in aiding a variety of problems related to low mood and stress by teaching problem-solving skills, assertiveness, tackling negative thinking and increasing activity levels [6,7]. This study looks at applying similar approaches in a back to work setting.

Results from this research will be used to indicate whether the online intervention is an acceptable resource for those aiming to get back to work. By assessing the acceptance and feasibility of the package for this population, we will be able to gain a key insight as to how such an intervention can be best delivered to individuals within this type of organisation.

There should be few harms or discomforts as the online classes use everyday language and address widely experienced life skills’ problems. No formal diagnosis of depression or anxiety is made at any stage. Since the intervention is a life skills package that will be introduced as part of the Remploy service, we do not expect any emergencies. Participants will receive care as usual from Remploy, and any deterioration in their condition will be managed according to the usual Remploy guidelines. [name] and [name] will also be available for consultation on such cases.

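### The stated population has low mood or depression, but the eligibility criteria contain no mood requirement, so people without symptoms can be randomised and counted

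*Protocol article*

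**What the plan says.** Three places in the protocol article describe who is to be studied. The abstract states: "Participants with symptoms of low mood will be recruited from the disability employment service, Remploy". The Aims section states: "The aim of this study is to recruit people experiencing symptoms of depression", and then: "We will include both those with clinically diagnosed major depression as well as those with raised mood scores". The Benefits to participants section refers to "adults who are out of work and experiencing mild to moderate symptoms of low mood".

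The Participants section gives the operative lists. Inclusion begins: "Participants will be willing to take up the offer of LL and appropriate for usual Remploy support". It adds no active risk to self at the initial assessment and the ability to register on the website and follow the materials. Exclusion covers people unwilling or unable to use the approach and people at active risk of suicide. Age 16 or over is stated beside the lists. Neither list mentions mood, a diagnosis or a questionnaire score.

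Under Procedure for recruitment and study setting, "All new candidates will be informed of the study". At the second appointment the consent form is collected, the baseline questionnaires are handed to administration staff, the case notes are marked, and an allocation envelope goes to the case loader. The Consent section says eligibility must be assessed before participation starts. The only contents it names for the eligibility pack are an information sheet and a consent form.

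**The concern.** The article gives explicit criteria and a step-by-step route to allocation, so the gap is not just a product of condensing a longer document. The intention stated in the Aims is missing from the place where eligibility is decided.

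Two results of the study depend on it. The first is feasibility of recruitment, which is part of the primary question. The Discussion judges it by a weekly count of participants, and as written that count can be met by people outside the stated population. The second is sample size for the future RCT. The Research questions, Follow-up data collection and Statistical analyses sections all point to efficacy data from this study as the input. A participant scoring 0–4 on the PHQ-9 can improve by at most 4 points, so such participants tend to pull the mean effect down and can shift the SD in either direction. If the later trial is aimed at people with low mood, its recruitment forecast would be too optimistic and its effect and SD would come from a different mix of people.

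**Working it through.** **1. Criteria against stated population.** Take a new candidate aged 16 or over with a PHQ-9 of 0–4, no depression diagnosis, no disclosed risk, willing to use the package and able to do so.

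| Source in the article | Is this person in? |
|---|---|
| Abstract (symptoms of low mood) | Not in the intended population |
| Aims (diagnosed depression or raised mood score) | Not in the intended population |
| Benefits to participants (mild to moderate symptoms) | Not in the intended population |
| Participants, inclusion list | Meets every item |
| Participants, exclusion list | Meets no item |
| Procedure, hand-in to envelope | No step that would stop them |
| Consent, eligibility assessed first | Can only apply the listed criteria, so passes |

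Baseline data collection presents the PHQ-9 as a baseline measure. The PHQ-9 section gives severity bands starting at 0–4 (minimal) and no entry threshold. The Aims wording on raised scores names no instrument, cut-off or time of assessment.

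**2. The plan's own recruitment figure.** About 100 people in 6 months: 100 / 26 weeks = 3.85 per week. In reverse, 3 × 26 = 78 and 4 × 26 = 104. The stated 3–4 per week reproduces, but it is a count of all participants, whatever their mood score.

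**3. Illustration of dilution.** The inputs here are assumed, not taken from the article. Let f be the share of randomised people who have symptoms. Suppose the effect is δ in them and zero in everyone else, and the SD is unchanged. The mean effect is then fδ. Since n per arm = 2(z₁₋α/₂ + z₁₋β)² SD² / (effect)², the required n is multiplied by 1/f².

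- f = 0.75: 1 / 0.5625 = 1.78
- f = 0.50: 1 / 0.25 = 4

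With an assumed δ of 0.5 SD, two-sided α of 0.05 and 80% power:

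- f = 1: 2 × (1.960 + 0.842)² / 0.5² = 62.8, so 63 per arm
- f = 0.75: 62.8 / 0.5625 = 111.6, so 112 per arm
- f = 0.50: 62.8 / 0.25 = 251.2, so 252 per arm

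If the later trial enrolled only symptomatic people, sizing it on the diluted effect would make it larger than it needs to be. The unchanged SD is a simplification, because mixing low scorers with symptomatic participants would generally alter it.

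**The case against.** **The Aims already state an inclusion intent, and the Consent section bars participation until eligibility is assessed.** Both are true. But an eligibility check can apply only criteria that exist, and the Aims sentence cannot be applied without an instrument and a cut-off. What stands is that the article never says the PHQ-9 goes unscored. A reader might infer from the order of events that the form is unread when the envelope is opened. The text supports only that no checking step is described.

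**Volunteers for such a package are likely to be symptomatic.** This is plausible, and it limits the likely size of the problem. Willingness favours people with symptoms but does not require any.

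**The employment variables, not mood, are called the main outcomes in the feasibility section of the Discussion, and mood falls under secondary outcomes.** This stands in part. It is not shown that the PHQ-9 would drive the future sample size, and a low PHQ-9 puts no floor on GAD-7, WSAS or employment. The Follow-up data collection section nevertheless ties the mood, social function and satisfaction data to that calculation. The recruitment point does not depend on which outcome is chosen.

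**The problem is recoverable.** Baseline questionnaires are collected before allocation, and the Aims promise a detailed description of mood severity, so low scorers will be visible. This is a good reason not to treat the point as fatal. It does not settle who counts towards the weekly threshold.

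**Conclusion.** The point holds as an inconsistency between the stated population and the listed criteria. It should be fixed, but it does not invalidate the study. That people without symptoms can be randomised and counted rests on the text alone. How many will be is unknown, so the 1.8-fold and 4-fold figures are illustrations under assumed shares, no effect in others and an unchanged SD.

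Three stronger readings are tempting but not supported:

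- A reader might take the Remploy section's "Of these, around one in four will have experienced stress or low mood at some point" as the symptomatic share and apply it to the dilution formula or the weekly recruitment threshold. That figure covers all clients of the Scottish branches and any past experience of stress or low mood. It is not current status, and it is not a rate among those who consent.
- A reader might see a contradiction between "experiencing mild to moderate symptoms of low mood" and the inclusion of major depression. The wordings differ and should be aligned, but they do not exclude each other.
- A reader might think the suicide-risk exclusion conflicts with the allocation sequence. The article places that exclusion at the initial assessment, before the second appointment, and says openly that risk is not routinely investigated. No contradiction is shown.

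**What to change.** 1. Carry the Aims definition into the inclusion criteria: a known diagnosis of depression or a raised baseline mood score. The investigators should choose the instrument and threshold from the measures already collected. A cut-off on the PHQ-9 alone would not match the Aims, because it would drop people with a known diagnosis who currently score low.
2. Add a step to the recruitment procedure that checks this criterion after the questionnaires are handed in and before the envelope is opened.
3. Reconcile the descriptions of the population in the abstract, Aims, Participants and Benefits to participants sections.
4. Report the recruitment rate, and judge it against 3–4 per week, for participants who meet the definition.
5. For the participants already entered (20 at the time of writing), take the mood-based sample-size inputs from those who met the definition at baseline. Membership of that subset is fixed before allocation, so the comparison of arms within it remains a randomised one.

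The cost is a short amendment and a scoring step at the second appointment. Recruitment will appear slower, and estimates from the subset will be less precise. With 20 of the planned 100 entered, most of the sample can still be recruited under the clarified criterion.
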